## 1.1.5 Maternal Health Status in Ethiopia

Levels of utilization of ANC, delivery and PNC have been steadily increasing in Ethiopia as
shown by DHS data between 2000 and 2019. The national averages in 2000 were 27% for ANC, 5% for delivery care and 11% for PNC (CSA, 2001) but increased to 74%, 50% and 34% respectively by 2019 (EPHI, 2019). Similar upward trends have been observed in the SNNP region, with ANC having the highest consumption and PNC having the lowest. While ANC use, when measured as at least one visit, has generally been higher than other service use in Ethiopia, it is much lower when the proportion of women reporting four or more visits is considered. Nevertheless, the number of women reporting at least four ANC contacts has increased between 2000 (10%) and 2019 (43%) (EPHI, 2019, CSA, 2001). Pregnant women have also tended to begin using ANC in their second trimester rather than in their first trimester as recommended, and this has only marginally improved over time (CSA, 2016). The proportion of births attended by skilled professionals has been on the rise since 2000 (CSA, 2016, CSA, 2001). However, the majority of these births are assisted by nurses and midwives rather than doctors. In 2016 for example, only 20% of births were attended by doctors although the proportion is much higher in private facilities compared to government facilities (CSA, 2016). A shift in policy around clean and safe delivery at health posts may also have affected the profile of providers attending to births. Initially HEWs were trained to support uncomplicated deliveries at health posts (Medhanyie et al., 2012, Jackson and Hailemariam, 2016), but this policy was later discontinued possibly over concerns about the inability of all HEWs to perform this safely (Desta et al., 2017). The percentage of women receiving PNC from health professionals has also been slowly rising from just 3% in 2000 to 16% in 2016 (CSA, 2001, CSA, 2016). Most women receive their first postnatal check within the first 48 hours after delivery and numbers have been steadily increasing from just 2% in 2000 (49) to 34% in 2019 (EPHI, 2019). As with ANC, very few women have additional PNC visits beyond the first 48 hours as recommended. In fact in 2016, less than 2% of women reported postnatal checks between one and six weeks after birth (CSA, 2016).

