## 4.5 Inclusion and Exclusion Criteria

**Inclusion criteria**

- Pregnant women less than 20 weeks gestational age
- Living in selected kebele
- Pregnant women willing to participate in the study

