**Step 4: End line data collection, analysis and report writing**

Step 2: Religious leaders’ training by project PI

Training contents: Maternal health message contents, flip chart, poster and group education

Trained religious leaders led SBCC to improve maternal health behavior

Figure 3. Presents the intervention processes and package of trained religious leaders led SBCC.

| Session | **Content of the message** | **Dose** | **Strategy of delivery** | **Frequency** | **Compliance parameters** | **Responsible person** |
| --- | --- | --- | --- | --- | --- | --- |
| Session 1 | - Major causes of maternal and new-born Illness and death | 1:00 hour | • Brain storming • Group education/ Group work • Case study/ case scenario • Question and Answer (Q&A) • Agree/ Disagree exercises • Group Presentation | Once at their 2^nd^ trimester period | -% pregnant mothers participated | Researcher and trained religious leaders |
| Session 2 | - Focused Antenatal Care - About danger signs during pregnancy | 1:00 hours | Brain storming • Group education/ Group work • Case study/ case scenario • Question and Answer (Q&A) • Agree/ Disagree exercises • Group Presentation | Once at their 2nd trimester period | -% pregnant mothers participated | Researcher and trained religious leaders |
| Session 3 | - Birth preparedness and complication readiness - Danger signs, labor and childbirth, - Components of postnatal care and Postnatal danger signs and neonatal danger signs | 1:00 hour | Brain storming • Group education / Group work • Case study/ case scenario • Question and Answer (Q&A) • Agree/ Disagree exercises • Group Presentation | Once at their 3^rd^ trimester period | -% pregnant mothers participated | Researcher and trained religious leaders |
| Session 4 |  | 1:00 hour | Brain storming • Group education / Group work • Case study/ case scenario • Question and Answer (Q&A) • Agree/ Disagree exercises • Group Presentation | Once at their 3^rd^ trimester period | -% pregnant mothers participated | Researcher and trained religious leaders |
|  | **Providing specific take-home print materials**   - ANC practices - SDS practice | -Poster  -Information card  -Flip chart | - | Delivered during in each training session | -% of pregnant mothers received print materials | Researcher and trained religious leaders |
|  | **End line data collection** | - | - | at 4^th^ month of intervention | % pregnant mother interviewed | Researcher, supervisors data collectors. |

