**Antenatal care service utilization**

Antenatal care service utilization will be measured based on “at least one ANC attendance” (Women who have attended at least one ANC check-up during their current pregnancy) and “four or more ANC attendance” (Women who attended four or more ANC visits) during their current pregnancy as reported by the participant.

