# APPENDICES

# **Annex 1: Questionnaire** for quantitative part

D**eveloped to collect baseline and end-line data for the project entitled** Effectiveness of trained religious leaders’ engagement in maternal health education on maternal health service utilizations: Evidence from cluster randomized controlled trial study in Misha District, Hadiya Zone, and Southern Ethiopia

General Information

Name of Kebele: ________________

Name of Gote __________________

House number ____________________

Family Id ____________________

Individual Id __________________

Date of interview: ____________time interview started _____________ ended at ____________

Respondent available on: 1. 1st visit.

2^nd^ visit.

3^rd^ visit.

Status of interview: 1. Completed. 2. Partially completed (refused in the middle).

Refused: 4. Candidate was absent in 3 visits:

11. Interviewer‘s name: --------------------------------------------Signature: -------------------

12. Supervisor who checked questionnaire for completeness and accuracy:

Name: --------------------------------------------Signature: -------------------------

Date-------------------------

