**PART III MATERNAL HEALTH SERVICE UTILIZATION**

| **Sir. No.** | **Questions** | **Responses** | **Skip to** |
| --- | --- | --- | --- |
| 301 | Is your current pregnancy planned? | 1. Yes 2. No |  |
| 302 | What was your feeling when you recognized your last pregnancy | 1. Happiness  2. Sadness  3. Nothing  4. Other (specify)_________________ |  |
| 303 | Did you face any health problem in this pregnancy? |  |  |
| 304 | If yes to Q 303, what were they? (*Do not read the choices*) | 1. Vaginal bleeding  2. Sever head ache  3. Face/ hand swelling  4. Persistent vomiting  5. Hypertension  6. Fit  7. Other (specify)_______________ |  |
| 305 | Did you visit a health facility during in this pregnancy? | 1. Yes  2. No |  |
| 306 | If yes to Q305, reason for visit | 1. Pregnancy related health problem  2. Health problems not related to pregnancy  3. For antenatal care  4. Other (specify) -------------------------- |  |
| 307 | Did you receive any antenatal care in this pregnancy? | 1. Yes  2. No |  |
| 308 | If you did not attend antenatal care, can you tell me the reasons? (Multiple answer is possible)  **(Do not read the choice)** | 1.No or little Knowledge about ANC  2. No health problem encountered  3. Health institution is too far from my home  4. Expense to ANC is unaffordable.  5.long waiting time  6.Poor handling by health care providers  7. Lack of transportation  8. Lack of time to go to health institution  9. Other (specify)---------------------- |  |
| 309 | If yes to Q 308, at what gestational age did you start pregnancy check-up? | 1. One to three months  2. Four to six months  3. Seven to nine months  4. I don‘t remember |  |
| 310 | How many times did you go for pregnancy check-up? | 1.One time  2.Two times  3.Three times  4.More than three times  5.Don't remember |  |
| 311 | To which institution did you go for  Antenatal care service? | 1. Hospital 2. Health center  3. Health station  4. Other (specify) ________________ |  |
| 312 | Why did you prefer this institution? | 1. Close to my house  2. Competent health worker  3. Fair price  Other (specify) _________ |  |
| 313 | Was health education given during each visit? | 1. Yes, always  2. Yes, sometimes  3. Not at all  4. Don‘t remember |  |
| 314 | If yes to Q 313, were you informed about danger  signs related to pregnancy | 1.Yes  2. No  3. Don‘t remember |  |

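### Both antenatal-care outcomes count visits made before any session; end-line adjustment for each woman's recorded baseline visits would recover power at no data cost

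*Protocol*

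**What the plan says.** The Protocol's operational definitions, repeated in section 4.16, give two ANC outcomes, both by self-report. One is "Women who have attended at least one ANC check-up during their current pregnancy"; the other is "Women who attended four or more ANC visits", also in the current pregnancy. Neither starts counting at enrolment or at the first session.

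The inclusion criterion in section 4.5 is "Pregnant women less than 20 weeks gestational age". Section 1.1.5 says of Ethiopia that "Pregnant women have also tended to begin using ANC in their second trimester rather than in their first trimester as recommended". ANC is taught in session 2, which section 4.13 places one month after session 1.

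The Annex 1 questionnaire serves both surveys. Q307 asks "Did you receive any antenatal care in this pregnancy", Q310 asks how many check-ups there were, and Q201 asks for months of pregnancy.

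Section 4.19 pools baseline and end-line data, follows intention to treat, allows for clustering, and adjusts for baseline differences through an interaction between study period and allocation. Table 4 names GEE for Objective 2. Neither place uses a woman's own earlier visits.

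**The concern.** Enrolment runs into the second trimester, when first visits are said to be usual, and the ANC session comes later still. Visits already made cannot be changed by the intervention, yet they count.

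For the any-visit outcome, a woman with a visit before enrolment is already a success whichever arm her kebele is in, apart from recall error at end line. For four or more visits, her earlier visits are only a head start, and the sessions can still decide the result.

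At stake is precision. The period-by-allocation interaction deals with differences between arms in their baseline proportions. It does not use the fact that a particular woman's end-line answer is already known, or partly determined, at baseline. That predictable variation stays in the error term, so Objective 2 has less power than its own data allow.

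**Working it through.** **The plan's own figure.** Section 4.8 sizes the trial for skilled delivery (26% versus 41%), not ANC. Its 155 per arm reproduces with a two-sided 5% test and 80% power; the stated one tail gives 122. Then 155 × 2 × 1.1 = 341, and 155 × 1.98 = 306.9, stated as 306. No power is given for ANC, so the rest is a scenario.

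**Inputs from the Protocol**
- Control attendance for at least one visit: 74% (section 1.1.5, national 2019 figure, used here as an assumption).
- 306 women per arm and ICC 0.02 (section 4.8); six clusters per arm (section 4.9), so 306/6 = 51 women per cluster.

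**Assumptions not in the Protocol**
- Share q with a visit before baseline: ranged from 10% to 40%.
- Effect among women with no earlier visit: 15 points. This borrows the size of the skilled-delivery effect.

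**Formulas for the any-visit outcome**
- Control rate among women with no earlier visit: (0.74 − q)/(1 − q). The intervention rate is this plus 0.15.
- All-women difference: (1 − q) × 0.15.
- Design effect for all women: 1 + (51 − 1) × 0.02 = 2.00.
- Design effect for women with no earlier visit: 1 + (51(1 − q) − 1) × 0.02.
- Power: two-sided 5%, pooled-variance z, normal approximation.

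**Why baseline attendance helps without dropping anyone.** Among prior attenders every outcome is a success in both arms, so that stratum adds no difference and no variance. The standardised difference is (1 − q) times the difference among the others, and its standard error is (1 − q) times theirs. Its z-value therefore equals that of the women with no earlier visit, while the estimate still refers to all women.

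**Example, q = 30%**
- Rates with no earlier visit: 0.44/0.70 = 62.9% versus 77.9%.
- Women per arm: 306 × 0.7 = 214.2. Design effect: 1 + (35.7 − 1) × 0.02 = 1.694. Effective number: 126.4.
- Standard error: √(2 × 0.7036 × 0.2964/126.4) = 0.0574.
- Standardised: difference 0.7 × 0.15 = 0.105, standard error 0.7 × 0.0574 = 0.0402, z = 2.61.
- Unadjusted: 74.0% versus 84.5%, effective number 306/2 = 153, standard error 0.0464, z = 2.26.

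| Share already attending | All-women difference (points) | SE unadjusted | SE standardised | Power unadjusted | Power standardised |
|---|---|---|---|---|---|
| 10% | 13.5 | 0.0451 | 0.0433 | 85% | 88% |
| 20% | 12.0 | 0.0457 | 0.0420 | 75% | 82% |
| 30% | 10.5 | 0.0464 | 0.0402 | 62% | 74% |
| 40% | 9.0 | 0.0470 | 0.0379 | 48% | 66% |

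A different variance form moves the 30% entry to about 75%. With a t reference on 10 degrees of freedom, which suits 12 clusters better, the power columns become 77/66/53/41% and 80/73/65/57%.

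**Four or more visits.** No matching figure can be given, because an earlier visit does not fix that outcome. The gain would depend on how well baseline count and gestation predict it, which the Protocol does not say.

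**The case against.** The case for leaving the plan alone is substantial.

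- **The definitions are the usual ones.** Section 1.1 gives at least one and at least four visits as the common ANC measures. If 30% have already attended, 10.5 points is the true effect among all women, not a distorted 15. This stands, and is why the definitions should stay.
- **The figures rest on assumptions.** The Protocol gives neither q nor an ANC effect. At q = 10% the gain is about 3 points. If the 15 points applied to all women and none had attended before, power would be about 92 to 93%. This stands as a limit on size.
- **Covariates are often left to the statistical analysis plan.** True, and if that plan already adjusts for baseline visits the point is met. But section 4.19 already says how baseline data enter, and Table 4 names the model.
- **Women may not be linked.** Sections 4.11 and 4.17 speak of repeat cross-sectional surveys. However, section 4.17 also says panel data, Figure 2 follows recruited women to end line, section 4.8 allows 10% loss to follow-up, and the questionnaire has an Individual Id. Linkage looks feasible once the wording is reconciled.

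A reader might also go further and restrict the any-visit outcome to women answering no to Q307 at baseline. The Protocol does not support that as the main analysis. It changes the question asked, and it selects women on a self-report taken after a public allocation (sections 4.15 and 4.17). Standardising gives the same gain with nobody excluded.

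**Conclusion.** The point holds as an efficiency improvement. Both outcomes count visits the intervention could not have affected, and the planned analysis does not use the baseline record woman by woman.

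Under the stated assumptions, using baseline attendance raises power for at least one visit by about 3 points if 10% had already attended and about 18 points if 40% had. The calculation also assumes that the ICC of 0.02 applies among women with no earlier visit and that prior attenders report consistently at end line. The gain for four or more visits is unquantified.

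Three stronger readings should not be drawn:
- **That Objective 2 is biased.** Visits before the sessions count alike in both arms, and the all-women comparison is randomised.
- **That prior attenders are certain successes on both outcomes.** This is true of at least one visit only. For four or more it would require four visits before enrolment.
- **That the baseline record is ignored.** It enters through the interaction term, but not at the level of the individual woman.

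**What to change.** In section 4.19 and Table 4, keep both all-women definitions and the intention-to-treat population. Analyse the end-line outcomes with adjustment for clustering, as follows:

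1. **At least one visit:** estimate the risk difference stratified by, or standardised over, baseline Q307. Do not simply add Q307 to a logistic model, because prior attenders would be perfectly predicted successes and its coefficient could not be estimated.
2. **Four or more visits:** add baseline visit count (Q310) and gestation at entry (Q201) as covariates.
3. **Supporting analysis only:** show the effect on at least one visit among women with none at baseline.
4. **Linkage:** state that the same women are followed and matched by Individual Id, and reconcile the repeat cross-sectional wording in sections 4.11 and 4.17.
5. **Timing:** state that Q307 and Q310 are recorded before the first session, since the baseline survey follows allocation.

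This is a free improvement: wording only, with no new question, visit or participant. It does depend on step 4; if women are not linked, steps 1 to 3 cannot be carried out.

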**Birth preparedness and complication readiness**

Birth preparedness: A woman will be classified as “well birth prepared” in the most recent pregnancy if she has accomplished three of the following practices: identified skilled health professional, saved money, identified transport or had delivery kit/materials. A woman who makes arrangements for birth in less than three of the four ways will be classified as “not well birth prepared”.

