**Neonatal Danger signs: (**Poor feeding or unable to suck**,** Diarrheal**,** Redness around the cord**,** Red eye/discharging eyes**,** Difficult breathing**,** Yellow coloration of the skin/jaundice**,** Hypothermia/shivering**,** Blisters on skin/Skin lesion**,** Baby doesn’t cry**,** Fever**,** Unconscious**,** Fast breathing**,** Chest in drawing**,** Doesn’t pass urine**,** Doesn’t pass stool and Convulsions.

**Consulting doctor or others health professionals:** if they have danger signs (during pregnancy, labor and childbirth, 42 days after delivery, and neonatal danger signs).

**Birth preparedness and complication readiness:** (plan for where to give birth, plan for a skilled birth attendant, plan to save money, plan for transportation and identification of compatible blood donors in case of emergency).

**Delivery at a health facility with a skilled provider** and **postnatal care:** (Women discuss FP method with husband Women adopted FP method after delivery Mother fed colostrum to the baby).

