## 4.19 Statistical analysis

Data of baseline and end-line surveys will be combined and analyzed using Stata 14.1. Analyses will be based on the intention-to-treat principle and compared differences of the outcomes between the intervention and control at both individual and cluster levels. First, Univariate analyses will be performed to explore the characteristics of respondents. We then will use logistic regression with random effects to estimate the effect of the intervention on prenatal behaviour, adjusting for clustering. Generalized estimated equations (GEE) regression analyses adjusted for clustering will be used to test the effect of the intervention on promoting maternal health behaviour. We will repeat analyses for the primary and secondary outcomes adjusted for baseline differences by fitting an interaction term between study period (baseline vs intervention) and allocation in each model. Mixed-effects multilevel logistic regression model will be used to identify determinants of birth preparedness and complication readiness.

**For qualitative study:** The interviews will be recorded and transcribed verbatim. The transcripts will be thematically analyzed using the qualitative software program Atlas.ti 6.0. Two analysts will independently code the transcripts and subsequently review, discuss, and refine the coding schemes until consensus will be reached. Emerging concepts will be assessed using the constant comparative method from grounded theory. This means that when this concept will be identified, previously analyzed interviews will be reviewed in order to check if their content fitted into this concept. A final version of the code book will be then developed leading to identification of themes, and sub-themes. Coded transcripts will be further analyzed and summarized in narratives for each theme and sub-theme. Study findings will be presented, discussed, and validated in a stakeholder meetings conducted in regional and district health offices.

| S.no | Research objectives | Study populations | Study design | Data source | Major outcome variables | Analytic model |
| --- | --- | --- | --- | --- | --- | --- |

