**የልደት ዝግጁነት እና ውስብስብ ዝግጁነት አካላት**

ችሎታ ያላቸው የጤና ባለሙያዎች፣ ተቋም ወይም የትውልድ ቦታ፣ መጓጓዣ፣ ፈንዶች፣ ደጋፊ ሰው፣ ውሳኔ ሰጪ እና በወሊድ ላይ ያሉ አደገኛ ምልክቶች::

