**Qarrimmina hassisso luwwa gudiissimmaa kee’maa’lli hawwi waroota’niimi gudimma**

Kuu guddimmi qaraamoo ciillichchi fayya’oominam ihukkoo ami fayya’omina horemi erisa awwaadookko.

Ku Qarrimmina hassisso luwwa gudiissimmaa amaadoo luwwi:

- Qariimmi bikkina losaakkoo mancho la’imma
- Qarakkam fayaa’oommi egechchi mine la’imma
- Qariimina marakkam amanina tiransporta gudisimma
- Qarammi amane maqire maroo manchoo hara’moo manna la’imma

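### The outcome named birth preparedness and complication readiness is scored on birth preparedness alone, from four practices that agree with neither the teaching lists nor the questionnaire

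*Protocol*

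**What the plan says.** **Definition.** The operational definition headed birth preparedness and complication readiness counts four practices: "identified skilled health professional, saved money, identified transport or had delivery kit/materials". Three are needed. "A woman who makes arrangements for birth in less than three of the four ways will be classified as" *not well birth prepared*. Nothing under the heading defines complication readiness.

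**Analysis.** Section 4.19 states: "Mixed-effects multilevel logistic regression model will be used to identify determinants of birth preparedness and complication readiness".

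**Teaching, English.** The key messages in section 4.13 list a place of birth, then "plan for a skilled birth attendant, plan to save money, plan for transportation and identification of compatible blood donors in case of emergency".

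**Teaching, Hadiyisa.** Section 4.13 makes Hadiyisa the language of the intervention. The Hadiyisa key-message sheet has four bullets on this topic, including "Qariimmi bikkina losaakkoo mancho" (apparently a person trained in delivery), "egechchi mine" (part of what appears to be the health facility) and "Qariimina marakkam amanina tiransporta gudisimma" (apparently transport). The fourth appears to concern people who accompany or help.

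**Teaching, Amharic.** The component list reads, in part, "ተቋም ወይም የትውልድ ቦታ፣ መጓጓዣ፣ ፈንዶች፣ ደጋፊ ሰው፣ ውሳኔ ሰጪ": apparently place, transport, funds, support person and decision maker. The preceding block appears to add extra costs and supplies for mother and newborn.

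**Questionnaire.** In Annex 1 Part IV, items 402 and 404 have boxes for transport, money, blood donor, skilled provider and support person.

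**The concern.** The variable carries a two-part name and measures one part. Any determinants reported from the 4.19 model would be read as applying to complication readiness, which the score does not contain.

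Secondly, the definition, the three language versions of the teaching and the questionnaire each use a different list. BPCR is one of the practices that the conceptual framework (section 2.9) expects the intervention to change. If the lists differ, a woman's score could depend partly on which text her religious leader worked from, and some of what she was taught would not be counted.

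Thirdly, the form as printed does not collect what the definition needs.

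**Working it through.** No sample-size or power figure enters this point, so there is no calculated figure to reproduce. The check is a count of scored practices covered by each text, set against the cut of three.

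The English columns come straight from the protocol. The Amharic and Hadiyisa columns are this review's reading.

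| Practice | Scored (operational definition) | English key messages (4.13) | Amharic sheet | Hadiyisa bullets | Part IV boxes |
|---|---|---|---|---|---|
| Skilled attendant | yes | yes | yes | yes | yes |
| Money | yes | yes | yes | no | yes |
| Transport | yes | yes | yes | yes | yes |
| Delivery kit or materials | yes | no | yes | no | no |
| Place of birth | no | yes | yes | yes | no |
| Blood donor | no | yes | no | no | yes |
| Support person or helper | no | no | yes | yes | yes |

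Scored practices covered (first four rows):

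- Hadiyisa bullets: attendant + transport = 2 of 4, below the cut.
- English key messages: attendant + money + transport = 3 of 4, meets the cut.
- Amharic sheet: attendant + money + transport + materials = 4 of 4, meets the cut.
- Part IV boxes: attendant + money + transport = 3 of 4 can be recorded; a kit could appear only under the free-text option.

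**Sensitivity to translation.** The title of the Hadiyisa block can be read literally as preparing the things needed for birth. If that counts as teaching materials, the Hadiyisa sheet covers 2 + 1 = 3 of 4. The same phrase appears just before as one topic in a list, so a topic name is the likelier reading. The range is therefore 2 to 3 of 4. On either reading, no bullet mentions money or a blood donor.

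**Complication readiness.** The only practice in the English list tied to an emergency is the blood donor. It is taught there and has a box in Part IV, yet it earns nothing in the score.

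**Opinion or practice.** The definition concerns arrangements the woman made. Item 402 asks for her view of what a woman can do; item 404 asks what the community provides. Neither records what she did. The numbering jumps from 402 to 404, so an item may have been dropped, but none that records practice is printed in Part IV.

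**The case against.** The strongest reply is that the Hadiyisa sheet is not the whole of the teaching. The English key messages are presented as the focus of the training, and following them gives 3 of 4. Sessions also use a facilitator manual and posters in the local language, whose content is not shown. The Amharic sheet covers all four scored practices, and item 809 of the engagement scale expects leaders to encourage women to plan for costs and supplies. All of this stands. A reader might infer that a woman who does everything she is taught is classed as unprepared. The documents do not support that: it would require the Hadiyisa bullets to be the entire curriculum and their title to carry no content.

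It can also be said that an outcome need not match the teaching item by item, particularly as section 4.16 takes the BPCR questions from an existing monitoring tool. That is fair; exact matching is a preference. It does not explain why the score omits the second half of its name, or why a scored item has no box on the form.

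Finally, BPCR carries limited weight. It is absent from the specific objectives, the hypothesis, the dependent variables in 4.7 and the design summary table; 4.7 lists it among the independent variables. The sample size rests on skilled delivery. This limits the importance of the point without removing it.

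**Conclusion.** The point holds in a limited form. Two parts rest on the English text alone. First, complication readiness has no scoring rule although 4.19 models it by name. Second, the scored list conflicts with the English key messages (place of birth and blood donor taught but unscored, kit scored but not on that list) and with Part IV (no kit box, no practice question).

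The third part is less certain. The Hadiyisa bullets appear to cover 2 of the 4 scored practices, or 3 if their title counts, against 3 for the English messages and 4 for the Amharic sheet. This assumes the readings above, which a Hadiyisa speaker should confirm.

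The effect on the share of women classed as well prepared cannot be quantified, because the protocol gives no uptake rates for these practices. The consequence is confined to the BPCR variable and the determinants model. The comparisons of skilled delivery, antenatal care and danger-sign knowledge are not affected by this scoring.

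**What to change.** 1. Reconcile the BPCR messages in the English key messages, the Amharic sheet and the Hadiyisa sheet so that every version teaches the same practices. The choice of practices is for the investigators.
2. Restate the scored practices and the cut-off in the operational definition so that they agree with that list.
3. Add Part IV items, in both questionnaire versions, that ask whether the woman herself made each scored arrangement.
4. Either add a complication-readiness component to the score, for which the blood donor is already in the English messages and has a box, or rename the outcome in 4.19 birth preparedness.

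The cost is small: rewording one definition, the message sheets and a few questionnaire items, with a translation check, before baseline.
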